# Can the prophylactic administration of tranexamic acid reduce the blood loss after robotic-assisted radical prostatectomy? Robotic Assisted Radical Prostatectomy with tranEXamic acid (RARPEX): study protocol for a randomized controlled trial

**DOI:** 10.1186/s13063-022-06447-x

**Published:** 2022-06-18

**Keywords:** Tranexamic acid, Robotic-assisted radical prostatectomy, Bleeding prophylaxis

## Abstract

**Background:**

The prophylactic administration of tranexamic acid reduces blood loss during procedures at high risk of perioperative bleeding. Several studies in cardiac surgery and orthopedics confirmed this finding. The aim of this prospective, double-blind, randomized study is to evaluate the effect of tranexamic acid on peri-and postoperative blood loss and on the incidence and severity of complications.

**Methods/design:**

Based on the results of our pilot study, we decided to conduct this prospective, double-blind, randomized trial to confirm the preliminary data. The primary endpoint is to analyze the effect of tranexamic acid on perioperative and postoperative blood loss (decrease in hemoglobin levels) in robotic-assisted radical prostatectomy. The additional endpoint is to analyze the effect of tranexamic acid on postoperative complications and confirm the safety of tranexamic acid in robotic-assisted radical prostatectomy.

**Discussion:**

No study to date has tested the prophylactic administration of tranexamic acid at the beginning of robotic-assisted radical prostatectomy. This study is designed to answer the question of whether the administration of tranexamic acid might lower the blood loss after the procedure or increase the rate and severity of complications.

**Trial registration:**

ClinicalTrials.gov NCT04319614. Registered on 25 March 2020

## Background

Prostate adenocarcinoma is the second most common malignancy in men. The incidence increases over time and with patient age. It is the second most common cause of death due to malignancy in men, after lung cancer. Standard treatment includes radical prostatectomy or radiotherapy in patients with life expectancy more than 10 years (LE1b, GRA) [1–3].

In recent years, there is a general tendency towards minimally invasive surgical procedures. In the treatment of localized prostate cancer, laparoscopic or robotic-assisted radical prostatectomy has become the standard treatment method. Despite tremendous development in the technology and technique of robotic-assisted radical prostatectomy (RARP) over more than 25 years, new ways and methods to improve oncological and functional outcomes are still needed [4–8].

Intraoperative blood loss is one of the most used parameters to assess the quality of surgical procedures. Rothermel et al. demonstrated that visual estimation of operative blood loss is unreliable and inaccurate [9]. Poletajev et al. concluded that blood loss during laparoscopic radical prostatectomy (LRP), which is considered comparable to the RARP, is clinically insignificant but can reach up to 600 ml, according to the laboratory findings [10].

Decreasing peri- and postoperative blood loss may lead to faster recovery after surgical procedures [11]. Sampaio et al. found five randomized prospective studies evaluating 838 patients with antifibrinolytics in cancer surgery. This meta-analysis found no evidence that antifibrinolytics increase the risk of thromboembolic complications. The authors have shown that it is effective in reducing total perioperative blood loss and also in the need for blood transfusion [12]. Several hemostyptic agents have been tested in this setting [13]. Hemostatic recombinant activated factor VII was originally developed to manage uncontrolled bleeding in hemophiliac patients. It has been used off label in cardiac surgery, neurosurgery, hepatic surgery, and open radical prostatectomy. Its use was associated with a higher risk of arterial thromboembolic events, especially in older patients, and therefore should not be used in prophylactic setting in order to reduce blood loss. Its high price disqualifies it from the routine use in urological procedures [14]. Antifibrinolytic aprotinin is a broad-spectrum inhibitor of serine proteases, including those in the coagulation cascade. It has been shown to have a better effect on the prevention of peri- and postoperative bleeding than tranexamic acid. However, in 2008, aprotinin was withdrawn from the market due to massive side effects, including increased perioperative mortality during complex cardiac surgery [15].

Tranexamic acid is an antifibrinolytic agent used to relieve bleeding. The mechanism of action lies in binding to plasma-free plasminogen with higher affinity than tissue plasminogen activator. It prevents its conversion to plasmin, which is responsible for the degradation of fibrin polymers. It results in greater stability of the fibrin clot at the site of bleeding, and therefore, it lowers blood loss [16–18]. The use of tranexamic acid during or after the procedure does not improve results, unlike administration prior to surgery. A biological explanation is that tranexamic acid may bind plasminogen in the early phase of the fibrinolytic cascade, after the beginning of the procedure, reducing tissue plasminogen activator activity up to 80% [19].

In urology, increased conversion of plasminogen to plasmin should occur, both by washing the tissue plasminogen activator from the destroyed tissue and by urokinase present in the urine [20]. Several studies did not confirm the positive effect of tranexamic acid in terms of reduced perioperative and postoperative blood loss in prostate transurethral resection [21, 22]. Other studies showed the positive effect in transurethral prostate resection [23, 24], open radical prostatectomy [25], and open radical cystectomy [26], including a recent meta-analyses [27, 28]. Due to the limited number of studies and the high heterogeneity of the results, more trials with a large number of patients are necessary to confirm these findings [28].

No study to date has tested the prophylactic administration of tranexamic acid at the beginning of robotic-assisted radical prostatectomy in a prospective manner. A Cochrane review concluded that randomized controlled trials different from cardiac surgery are needed to assess the efficacy and safety of tranexamic acid in surgical procedures [13].

## Methods/design

The RARPEX trial is designed as a randomized, placebo controlled, surgeon- and patient-blinded superiority single-center study with two parallel groups. Randomization will be performed as a block randomization with 1:1 allocation.

### Objectives and hypothesis

The primary aim of the Robotic **A**ssisted Radical Prostatectomy with EXacyl (RARPEX) trial is to investigate the effect of tranexamic acid on perioperative and postoperative blood loss (decrease in hemoglobin levels) in robotic-assisted radical prostatectomy.

H0: The drop of hemoglobin level after the procedure is similar in both groups.

HA: The drop of hemoglobin level after the procedure in control group is higher than in study group.

Additional endpoint of the RARPEX trial is to analyze the effect of tranexamic acid on postoperative complications and confirm the safety of tranexamic acid in robotic assisted radical prostatectomy.

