### Sample size calculation

The sample size calculation is based on the data from our pilot study [29]. We used two-sample *T* tests allowing unequal variance with respect to the primary endpoint, which is the difference in hemoglobin level drop on postoperative day (POD) 1. The level of significance is set to 5 g. With *α* = 1% and *β* = 10%, a sample size of 64 patients per group is necessary to detect a clinically significant difference between the groups. With an expected dropout rate over 33%, we plan to enroll 200 patients in the study.

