### Primary and secondary endpoints

The primary endpoint is to analyze the effect of tranexamic acid on perioperative and postoperative blood loss in a randomized and prospective manner. A clinically significant difference between the groups on POD 1 is set to 10 g/l. The sample size was calculated for this setting.

The additional aim of the RARPEX trial is to analyze the effect of tranexamic acid on other postoperative complications: wound infection, intraabdominal collections, urinary leakage, delayed gastro-intestinal emptying, postoperative hemorrhage, pneumonia, and abdominal rupture, especially analyzing the incidence of cardiac events and venous thromboembolism (VTE) after the procedure (Table 1).

**Table 1 Tab1:** Clinical parameters and postoperative complications for analysis

Parameters	Definitions
Hospital stay	Days from initial operation to hospital discharge plus any readmission within 30 days
Console time	Time of console surgeon activity (min)
Postoperative hemorrhage	Evidence of blood loss from drains, based on ultrasonography or CT
Transfusion rate	The number of blood transfusions
Urinary leakage	Evidence of creatinine level > 500 μmol/l and volume of the drain output exceeds 200 ml/24 h, confirmed on cystography
Lymphorrhea	Evidence of creatinine level < 500 μmol/l, hematocrit < 0.2, and volume of the drain output exceeding 200 ml/24 h, no urinary leakage on cystography
Intraabdominal fluid collection	Collection of fluid measuring ≥ 3 cm associated with clinical or laboratory abnormalities
Symptomatic fluidothorax	Fluid in the pleural cavity associated with respiratory distress or a need to evacuate the fluid
Thromboembolism	Unilateral limb swelling, acute respiratory insufficiency, based on ultrasonography or CT
Myocardial infarction	Increase of serum concentration of CK-MB and troponin and/or the following ECG changes: new Q waves ≥ 0.04 in duration, new persistent ST elevation, and/or depression
Brain stroke	Presence of neurological symptoms, findings on CT scan or MRI
Pneumonia	Presence of a new infiltrate on chest X-ray, as well as the following: body temperature > 38 °C, abnormal elevation of WBC, or positive sputum, and requiring antibiotic treatment
Acute renal failure	Serum creatinine > 300 μmol/l and/or need for dialysis
Wound infection	Surgical site infection associated with laparotomy that develops during the initial hospital stay

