Urinary tract infection	Culture-positive urine, pyuria, or bacteriuria on urinalysis requiring antibiotic treatment

*CK-MB* creatine kinase MB isoenzyme, *ECG* electrocardiogram, *WBC* white blood cells, *CT* computer tomography, *MRI* magnetic resonance imaging

Postoperative complications are graded based on severity according to the Clavien-Dindo definition (Table 2) [33].

**Table 2 Tab2:** Complication grades according to the Dindo-Clavien classification scheme

Grade	Definition
Grade I	Any deviation from the normal postoperative course without the need for pharmacological treatment or surgical, endoscopic, and radiologic intervention
Grade II	Requiring pharmacological treatment with drugs other than those allowed for grade I complications
Grade III	Requiring surgical, endoscopic, or radiological intervention
Grade IIIa	Intervention not under general anesthesia
Grade IIIb	Intervention under general anesthesia
Grade IV	Life-threatening complications requiring intensive care unit management
Grade IVa	Single-organ dysfunction
Grade IVb	Multiorgan dysfunction
Grade V	Death of the patient

We plan to seek for adverse events with repetitive blood sampling and imaging to prevent the underreported frequency of these events. But we are aware that the incidence is low, and our data will might not have sufficient power to make a definitive conclusion about safety.

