### Complications

Although transfusion rates after open retropubic radical prostatectomy (RRP) are low - 3.4%, and robotic approach dropped the rate even lower to 0.8% [42], in our pilot study to 1.0% [29]. The safety of homologous transfusion has improved over time, but the possibility of having transfusion-related reactions or acquiring transfusion-transmitted diseases still remains [43]. Concerns have been raised about the possible relationship between the administration of blood derivatives and an increased risk of relapse of malignancy and tumor-specific mortality [44, 45]. At this moment, we are aware of only one retrospective study showing a poor correlation between postoperative hemoglobin assessment and transfusion requirement among patients undergoing minimally invasive radical prostatectomy [36]. Prospective data is lacking.

Radical prostatectomy is associated with a higher risk of thromboembolism. Open radical prostatectomy has a considerably higher risk of thromboembolic events (1.0—15.7%) compared to robotic (0.2–3.7%) and laparoscopic (0.4–6.0%) approaches [46]. Administration of antifibrinolytics, which potentially increase the risk of thromboembolism in laparoscopic surgery for pelvic malignancy, may seem too risky. According to the literature data from recent meta-analyses, no demonstration of an increased risk of thromboembolism following treatment with tranexamic acid was observed [27, 28].

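### The stated aim of confirming safety conflicts with the protocol's own caveat and with a trial of about 100 patients per arm sized on hemoglobin drop only

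*Protocol article*

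**What the plan says.** The Protocol article gives the safety aim in several places, and they do not agree.

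- **Objectives and hypothesis:** the additional endpoint is to analyze complications and to "confirm the safety of tranexamic acid in robotic assisted radical prostatectomy". The Methods/design part of the Abstract has the same clause. The only formal hypotheses in this section concern the drop in hemoglobin.
- **Primary and secondary endpoints:** the aim is to analyze the effect on postoperative complications, with particular attention to cardiac events and venous thromboembolism. After Table 2 the section says the incidence is low and adds that "our data will might not have sufficient power to make a definitive conclusion about safety".
- **Abstract, Discussion:** the question is put neutrally, as whether the drug might raise the rate and severity of complications.
- **Methods/design:** a superiority trial. "Randomization will be performed as a block randomization with 1:1 allocation".
- **Sample size calculation:** based on the POD 1 hemoglobin drop. "With *α* = 1% and *β* = 10%, a sample size of 64 patients per group is necessary", and "With an expected dropout rate over 33%, we plan to enroll 200 patients in the study".
- **Discussion, Complications:** the thromboembolism rate for the robotic approach is given as 0.2–3.7%.
- **Statistical methods:** names a safety set analyzed by treatment received and a general threshold of P < 0.05, but no test for complications.

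**The concern.** To confirm safety is to reach a definitive conclusion about it, which is what the endpoints section says the data may not permit. The unqualified promise stands in the abstract and the objectives, the places against which the results will be read. The qualification comes only after a table later in the article.

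A confirmatory safety claim needs either a stated amount of excess risk to be ruled out or enough events to estimate the risk closely. The article states no safety hypothesis, and the trial's size was not chosen with complications in mind. The outcomes at issue are those that the article itself treats as the main worry with an antifibrinolytic in this surgery. At stake is therefore what may be concluded about harm, not the validity of the primary comparison.

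**Working it through.** **1. The plan's own figure.** The article states 64 per group for the hemoglobin endpoint and no figure for safety. The 64 cannot be reproduced: no standard deviation is given, and the target difference appears both as 5 g (Sample size calculation) and as 10 g/l (Primary and secondary endpoints). With n = 2·SD²·(z₀.₉₉₅ + z₀.₉₀)²/Δ², 64 per group implies an SD of about 7.3 for Δ = 5 or 14.7 for Δ = 10, taking α = 1% as two-sided. Nothing below depends on this. It shows only that complications played no part in the sizing.

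**2. Patients per arm.** 200 enrolled at 1:1 gives 100 per arm. The evaluable target is 2 × 64 = 128, and 1 − 128/200 = 36%, in line with the stated dropout of over 33%. I use 100 per arm as the favorable case and 64 as the lower bound.

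**3. Expected events.** At 0.2% to 3.7%, 100 patients yield 0.2 to 3.7 events per arm. At 0.2% in both arms, the chance of seeing no event at all is 0.998²⁰⁰ = 67%.

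**4. What zero events would show.** The exact two-sided 95% upper limit for 0/n solves (1 − p)ⁿ = 0.025.
- n = 100: 1 − 0.025^(1/100) = 3.6%
- n = 64: 1 − 0.025^(1/64) = 5.6%

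The limit of 3.6% is 3.6/0.2 = 18 times the lower quoted rate and almost equal to the upper one. A treated arm with no events at all would exclude almost none of the quoted range.

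**5. Power to detect harm.** The article gives no safety effect size and no test for complications. As my own assumptions I take the quoted range as the control rate, a doubling or tripling as illustrative effects, and a two-sided 5% Fisher test. Power is the sum over all pairs (i, j) of Bin(i; 100, p₀) × Bin(j; 100, p₁), counting the pairs with Fisher P ≤ 0.05.

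| Control rate | Power, doubling | Power, tripling |
|---|---|---|
| 0.2% | 0.0% | 0.0% |
| 1% | 0.6% | 3.4% |
| 2% | 4.4% | 17.1% |
| 3.7% | 12.7% | 42.6% |

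The normal approximation is kinder but leads to the same conclusion: 4% to 21% for a doubling across the range. With 64 per arm, Fisher power for a doubling is 0% to 6%.

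**6. The same point in events.** With no control events, 5 events among 100 treated patients give Fisher P = 0.059 and 6 give P = 0.029.

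**7. Size that a doubling would need.** For 80% power (normal approximation, two-sided 5%), 11,737 per arm at 0.2% and 600 per arm at 3.7%.

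**8. Precision of an estimate.** If both arms truly had 3.7%, the approximate 95% half-width for the risk difference would be 1.96 × √(2 × 0.037 × 0.963/100) = 5.2 percentage points.

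**The case against.** The strongest reply is that the article already says this. The endpoints section admits that power may be insufficient for a definitive safety conclusion, and the neutral statements of the aim outnumber the confirmatory ones. On that view, one verb in two sentences is loose. This stands in large part and is why the severity is low. It does not remove the point: the caveat was added without rewording the objective, so the two still disagree.

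A second reply is that the figures rest on choices the article does not make: Fisher's test, two-sidedness, and a doubling of risk. That is true, and they are labelled as assumptions. The zero-event limit needs none of them, and low power for a doubling holds across the whole quoted range under either calculation.

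A third is that the method for comparing complications belongs in an analysis plan that is not shown. That is also fair, and its absence here is not counted as a fault.

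A reader might infer something stronger: that the plan would take P > 0.05 on complications as the promised confirmation. The document does not support this. Statistical methods names no test for complications, its 0.05 threshold is general and is not a rule for declaring safety, and the endpoints caveat points the other way.

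**Conclusion.** The inconsistency is real and of low severity. The abstract and the objectives promise a confirmation that the endpoints section doubts and that a superiority trial of this size cannot give at the thromboembolism rates it quotes. The conclusion rests on about 100 patients per arm and on the quoted robotic range applying to this trial's control arm. Fewer evaluable patients would only weaken the safety evidence further. The exact power figures depend on the assumed test and effect; the conclusion does not.

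The primary endpoint, randomization, safety data collection and safety set are not affected. Trial status expected recruitment to finish by February 1, 2022, before the article appeared in June 2022, so the consequence lies in how the safety results are described.

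**What to change.** In the Abstract (Methods/design) and in Objectives and hypothesis, replace the confirmation clause by: *estimate the incidence of thromboembolic, cardiac and other complications in each arm*. This brings both places into line with Primary and secondary endpoints.

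Add one sentence: *Arms will be compared by risk difference with 95% confidence interval in the safety set, and a non-significant difference will not be reported as evidence of safety.* If an analysis plan already contains this, a reference to it is enough.

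The cost is wording, and a safety claim more modest than the abstract now makes. No patients, data or procedures are added. If recruitment has closed, the same wording can be used in the analysis plan and the results report.

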### Study population and eligibility criteria

All patients who are scheduled for operation due to low or intermediate risk prostate cancer in our institution will be screened and assessed for eligibility.

Only patients who will undergo robotic-assisted radical prostatectomy with suturing of dorsal complex vein (DVC) bundle at the beginning of the procedure without pelvic lymph node dissection will be included in the study. Patients with non-standard procedures or a procedure associated with higher morbidity will be excluded from the study to achieve a homogeneous study group.

Detailed inclusion and exclusion criteria are described below.

The following are the inclusion criteria:Patient scheduled for robotic-assisted radical prostatectomy without pelvic lymph node dissectionSigned informed consent providedBody mass index ≤ 35Age of patient ≤ 75 yearsOperating surgeon with experience of more than 100 cases

The following are the exclusion criteria:Body mass index > 35Age of the patient > 75 yearsCoagulation disorder (congenital or iatrogenic due to the chronic use of anticoagulants)Thromboembolic, cerebral, or an acute coronary event within the 6 months prior to prostatectomyChronic renal insufficiency (arbitrary cutoff level of creatinine 200 μmol/l)Allergic reaction to tranexamic acidOperating surgeon with experience < 100 casesPatient participating in another study

If subjects do not meet the inclusion criteria or withdraw their consent, they will be excluded from the study. The researcher will record the reason for their withdrawal.

#### Criteria for discontinuing

A trial participant should terminate intervention if they wish to do so or if the investigator judges it necessary due to any of the following reasons:Withdrawal of informed consentPatient refusal or non-compliance to the protocolOccurrence of an unexpected serious adverse effectNon-standard procedure (non-sutured dorsal vein complex in the beginning of the procedure, rectal, small bowel, or ureteral wall injury)Other hemostyptic drug or material used during or after the procedure

### Sample size calculation

The sample size calculation is based on the data from our pilot study [29]. We used two-sample *T* tests allowing unequal variance with respect to the primary endpoint, which is the difference in hemoglobin level drop on postoperative day (POD) 1. The level of significance is set to 5 g. With *α* = 1% and *β* = 10%, a sample size of 64 patients per group is necessary to detect a clinically significant difference between the groups. With an expected dropout rate over 33%, we plan to enroll 200 patients in the study.

### Ethics, study registration, and consent

This trial was approved by the independent ethics committee at the University Hospital Hradec Kralove (registration number 201903 I90P). The RARPEX trial will be conducted in the context of Good Clinical Practice and in accordance with the Declaration of Helsinki. The trial is registered at ClinicalTrials.gov under the registration number NCT04319614. All patients who are scheduled for robotic-assisted radical prostatectomy in our institutions will be screened for eligibility and informed in detail about the RARPEX trial. Informed consent will be obtained from each participant. The study procedures, risks, benefits, and data management will be clarified with the patients before they are asked to give their informed consent to participate. Any participant in this study may withdraw consent or voluntarily cease to participate at any time for any reason.

